### Data analysis

Data will be stored without identifying variables. It will be analyzed using SPSS 21.0 (SPSS Inc., Chicago, IL). Descriptive statistics will be used to describe the sample in terms of demographic profiles. The main outcome variable is PTSD diagnosis according to the CAPS, at 12 months posttreatment. Secondary outcomes include the severity of PTSD symptoms and depression symptoms.

The statistical analyses will be performed on the data of those participants who had participated in the pretreatment telephonic interview and in at least one follow-up wave. The principle method of data analysis will be a conditional latent class growth modeling with covariates (Bollen & Curran, 2006) using the Mplus version 7.2 software (Muthén & Muthén, 1998–2011). This method allows for comparing the trajectories of change in each of the five outcome variables between the two experimental groups while considering for possible preexisting differences in background characteristics. If the trial results are compatible with the research hypotheses, we expect the intercepts (the initial levels) of the growth curves in both groups to be identical and the slopes in the intervention group to be steeper than in the control group, indicating larger improvement in symptoms in the former group. We will use an estimation method such as full-information maximum likelihood to take advantage of all available data in presence of missing values. In case that the data will be non-normally multivariately distributed, as tested by Mardia's statistics, we will use estimation with robust standard errors (Little & Rubin, 2002) and corrected chi-square values. In the analyses, appropriate adjustments will be made for the permuted-block design of the trial sample.

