**Method:**

Two hundred patients arriving to a Level 1 emergency department following a motor vehicle accident will be randomly assigned to either treatment or control groups. Inclusion criteria are age 18–65, PTSD symptoms 2 weeks posttrauma related to current trauma, no suicidality, no psychosis. Patients will be assessed by telephone by a team blind to the study group, on four occasions: before and after treatment, and 6 and 12 months posttreatment. The primary outcome is PTSD symptoms at follow up. Secondary outcomes include depression and cost effectiveness. Analyses will be on an intention-to-treat basis.

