## Current study

The intervention used in this study—i-VR (Internet-VR)—was specifically designed as an intervention for PTSD that combines the two platforms described here, creating a VR environment that can be accessed via the Internet. Both the therapist and the patient will concurrently occupy the environment, even though they are not in the same physical place. This is illustrated in Fig. 1. The i-VR platform will be easier to access than other cyberspace environments. The intervention includes evidence-based components for PTSD, such as breathing retraining, exposure, and cognitive restructuring. It is a five session protocol, similar to those that have been used in other early intervention studies for PTSD (Bryant et al., 1999). This randomized controlled trial (RCT) will examine the following hypotheses:i-VR CBT will be more effective at reducing PTSD symptoms than the waitlist control, such that they will have lower PTSD levels at all follow-up assessments.i-VI CBT will result in less use of health services and fewer missed work days than the waitlist control.Patients who spend more time using the i-VR environment between sessions will benefit more from the treatment.

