### Sample size

Given previous research studies carried out at with this population, it is reasonable to assume that the following numbers will be applicable for this study (Shalev et al., 2011). Over 18 months, there will be 600 valid cases (that match the aforementioned inclusion and exclusion criteria). Of these, approximately 33% will have sufficient symptoms at 2 weeks posttrauma. This will give 200 valid cases, and assuming 50% attrition rate, this will leave 100 subjects, 50 in the treatment group and 50 in the waitlist control group. Assuming 30% spontaneous recovery rates in the waitlist group and 70% recovery rate in the Internet intervention, an alpha of 0.05 and power of 0.95, a total group size of 64 is needed.

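### The article names two conflicting primary outcomes, and its principal slope analysis does not isolate the 12-month diagnosis or match the contrast that was powered

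*Protocol article*

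**What the plan says.** Four places in the article bear on what the trial is meant to show.

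- Abstract, Method paragraph: "The primary outcome is PTSD symptoms at follow up". No scale and no single time point are given.
- Current study, first hypothesis: patients given i-VR CBT will do better than waitlist, "such that they will have lower PTSD levels at all follow-up assessments".
- Sample size: "Assuming 30% spontaneous recovery rates in the waitlist group and 70% recovery rate in the Internet intervention", with "an alpha of 0.05 and power of 0.95, a total group size of 64 is needed". Recovery is neither defined nor dated.
- Data analysis: "The main outcome variable is PTSD diagnosis according to the CAPS, at 12 months posttreatment". The next sentence reads "Secondary outcomes include the severity of PTSD symptoms and depression symptoms".

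On method, Data analysis says: "The principle method of data analysis will be a conditional latent class growth modeling with covariates". The model is applied to five outcome variables that are not listed. The expected pattern is equal starting levels in the two arms and a steeper slope under intervention, read as greater symptom improvement. Multivariate normality is to be checked with Mardia's statistics.

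**The concern.** Symptom severity is primary in the Abstract and secondary in Data analysis, so the two statements cannot both stand. The difference has consequences, because Research tools says that CAPS-5 yields both a diagnosis and a continuous score, and the two can give different answers.

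The analysis does not settle the matter. A steeper symptom slope across four assessments answers a different question from whether fewer treated patients have PTSD at 12 months. A reader of the results could be given a slope difference as the main finding when diagnosis at 12 months is similar in the two arms, or the opposite. Without one named primary outcome and a test tied to it, nothing in the article says which result decides. The stated power of 0.95 belongs to a comparison of proportions that the analysis section does not name.

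**Working it through.** **1. Reproduce the plan's own figure.** Inputs from Sample size: p1 = 0.30, p2 = 0.70, alpha 0.05, power 0.95. The 64 is read as the total over both arms. Assumption: 1:1 allocation, as implied by 50 and 50 remaining.

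Formula, per arm: n = [z_alpha × √(2 × p̄ × (1 − p̄)) + z_beta × √(p1(1 − p1) + p2(1 − p2))]² / (p2 − p1)²

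Here p̄ = 0.50, √0.50 = 0.7071, √(0.21 + 0.21) = 0.6481, z_beta = 1.645 and (0.40)² = 0.16.

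- One-sided 0.05: (1.645 × 0.7071 + 1.645 × 0.6481)² / 0.16 = (2.229)² / 0.16 = 31.1, so 32 per arm and **64 in total**. This matches.
- Two-sided 0.05: (1.960 × 0.7071 + 1.645 × 0.6481)² / 0.16 = (2.452)² / 0.16 = 37.6, so 38 per arm and 76 in total.

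The arcsine formula at one-sided 0.05 also gives 64. The stated size is thus what a comparison of two independent proportions produces. The unstated sidedness is a separate, smaller point.

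**2. Are there enough patients for that comparison?** Sample size expects 50 per arm after attrition. Power = Φ[(0.40 × √n − z_alpha × 0.7071) / 0.6481].

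- n = 50, two-sided: (2.828 − 1.386) / 0.6481 = 2.226, power **98.7%** (one-sided 99.5%).
- n = 32, two-sided: (2.263 − 1.386) / 0.6481 = 1.353, power 91.2%.
- n = 50 with Fisher's exact test, two-sided: 97.9%.

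**3. Set outcome, powered contrast and test side by side.**

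| Where | Quantity | Type | Time |
|---|---|---|---|
| Abstract | PTSD symptoms | not stated | follow-up, unspecified |
| First hypothesis | PTSD levels | not stated | every follow-up |
| Sample size | recovery | proportion | not stated |
| Data analysis, main outcome | CAPS diagnosis | binary | 12 months |
| Data analysis, principal method | slope of symptom improvement | trajectory | all waves |

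The last row bears on the Abstract's outcome. It does not isolate the fourth row, and it is not the contrast in the third.

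**4. Can a slope and a later difference disagree?** An illustration with assumed mean severities, not figures from the article. Take months 0, 2, 7 and 13; treated 40, 15, 14, 13; waitlist 40, 30, 22, 15. Treated patients are better at every follow-up, but by only 2 points at the last.

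- Straight lines with free intercepts: mean time 5.5, sum of squared deviations 101. Slopes are −154 / 101 = −1.52 (treated) and −179.5 / 101 = −1.78 (waitlist) per month. The treated slope is flatter.
- Both intercepts fixed at 40: sum of squared times 4 + 49 + 169 = 222. Slopes are −583 / 222 = −2.63 (treated) and −471 / 222 = −2.12 (waitlist). The order reverses.

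Under these assumed means the slope verdict depends on the form of the model, and neither version measures the difference at the last visit. Early gain followed by waitlist catch-up is a plausible shape here, since the article's introduction says that most people with early symptoms recover naturally.

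**The case against.** The strongest reply is that this is a condensed article. It calls the growth model the principal method, not the only one, and it also mentions SPSS, so a simple comparison of diagnosis may be planned elsewhere. Diagnosis may be among the five unlisted variables, and growth models can take binary outcomes. The Mardia check does not prove that every modelled outcome is continuous.

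Much of this stands as a limit on wording: one can say only that the article names no comparison of 12-month diagnosis, not that none will be done. It does not remove the point. The article itself fixes a primary outcome twice, a powered contrast and a principal method, and these disagree; further detail elsewhere would not make the Abstract and Data analysis agree. If diagnosis is modelled, a slope over all waves is still not the 12-month contrast. Moreover, Participants requires PTSD symptoms on every criterion except duration, so diagnosis would hardly vary at entry.

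A reader might also infer more than the text supports:

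- That there are three rival primary outcomes. Only the Abstract and Data analysis use a primary or main label. The first hypothesis sets a target, and the recovery rates are compatible with a diagnosis outcome.
- That the false-positive rate is inflated by a calculable amount. The article lists no set of competing tests to count, and requiring benefit at every follow-up is a stricter criterion, not an extra route to success.
- That Sample size already uses CAPS diagnosis at 12 months. It mentions neither.

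**Conclusion.** The point holds as a contradiction between two labelled primary outcomes, together with a principal analysis that matches neither the 12-month diagnosis nor the powered comparison of proportions. It should be corrected before data are analysed, because the main conclusion could depend on which statement is followed.

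It would be wrong to conclude that the trial is too small. For 30% against 70%, 50 per arm keeps two-sided power near 98.7%, and 95% power is retained if treated recovery is as low as about 65%. Those figures assume that the article's 50 per arm are reached and that its waitlist rate of 30% applies to the outcome finally chosen. No comparable figure can be given for the slope analysis, since the article supplies no variance, correlation or slope difference.

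**What to change.** - Make CAPS-5 PTSD diagnosis at 12 months after treatment the single primary outcome throughout. The basis is the explicit ranking in Data analysis.
- In Sample size, define recovery as absence of that diagnosis at 12 months, confirm that 30% and 70% are still the rates intended, and state the sidedness of the test.
- In Data analysis, name a between-arm comparison of that diagnosis as the primary test. One suitable form is a logistic model with arm and the two factors balanced at randomisation (gender and initial PTSD level), reporting the risk difference with a 95% confidence interval.
- Keep the growth model of CAPS severity, with its planned full-information maximum likelihood, as a secondary analysis, and list the five variables.
- Align the Abstract and the first hypothesis, making the all-follow-ups target secondary.

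The cost is wording in four sections plus one standard model. No extra patients or assessments are needed, because CAPS is already scheduled at 12 months.

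### The Abstract promises intention-to-treat, but the Data analysis section drops randomised patients with no follow-up wave, which can bias the planned slope comparison

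*Protocol article*

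**What the plan says.** - **Abstract, Method:** on size and allocation the article states "Two hundred patients arriving to a Level 1 emergency department following a motor vehicle accident will be randomly assigned to either treatment or control groups", and on the analysis principle "Analyses will be on an intention-to-treat basis".
- **Data analysis:** the statistical analyses use the data of "those participants who had participated in the pretreatment telephonic interview and in at least one follow-up wave". No exception and no second analysis set is described. The main method is a growth model with covariates. Its treatment contrast is the slope, and the initial level is the intercept, expected to be the same in both arms. Full-information maximum likelihood (FIML) is planned "to take advantage of all available data in presence of missing values".
- **Sample size:** "assuming 50% attrition rate, this will leave 100 subjects, 50 in the treatment group and 50 in the waitlist control group".
- **Procedure:** the CAPS-5 and SCID interview comes before entry to the trial. Follow-up interviews take place 2 weeks after treatment ends and again 6 and 12 months later.

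**The concern.** The requirement of a pretreatment interview is harmless, because that interview precedes randomisation. The requirement of at least one follow-up wave is not, because it selects on something that happens after allocation. The arms differ in ways that could affect it. The Procedure gives i-VR patients a laptop, training and five therapist sessions, while waitlist patients complete weekly web questionnaires. The Discussion says that uptake of the treatment is untested.

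FIML does not repair this as the text stands. The restriction defines the data first, so FIML fills in missing waves only for patients already in the set. Patients with a baseline interview and nothing afterwards carry information about how loss relates to initial severity, and they are removed before the likelihood is formed. Randomisation then no longer protects the equality of intercepts that the plan expects. A reader told that the analysis is intention-to-treat would not know this.

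**Working it through.** **1. The plan's own figures.** 200 × (1 − 0.50) = 100, or 50 per arm, as stated. The Sample size section's total of 64 (30% vs 70% recovery, alpha 0.05, power 0.95) reproduces with a one-sided alpha:

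n per arm = [1.645·√(2·0.5·0.5) + 1.645·√(0.21 + 0.21)]² / 0.4² = (1.163 + 1.066)² / 0.16 ≈ 31.1, rounded up to 32, total 64.

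With 50 per arm, power is 98.7% even two-sided. Power is therefore not the issue here; selection is.

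**2. How many could be excluded.** The rule drops only patients with none of the three follow-up waves. If all attrition occurs before randomisation, or every lost patient was seen at least once, the number is 0. If all of the 50% is post-randomisation loss with no wave at all, it is 100 of 200. The documents do not narrow this range.

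**3. Effect on the slope contrast (assumed inputs).** Take baseline X and 12-month score Y as standard normal, higher being worse, with correlation ρ and no treatment effect. In the i-VR arm a share a is retained below the baseline median and a share b above it. Waitlist retention is 50% throughout. Only two time points are used, to keep the algebra visible. The mean of X below its median is −0.798, so among retained i-VR patients:

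- baseline mean m = −0.798·(a − b)/(a + b)
- 12-month mean = ρ·m
- change = (ρ − 1)·m, against 0 in the waitlist arm

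With a = 0.7, b = 0.3, ρ = 0.5:

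- m = −0.798 × 0.4 = −0.319 SD, so the intercepts are unequal
- 12-month mean = −0.160 SD, so the raw 12-month comparison appears to favour i-VR by 0.16 SD
- change = −0.160 − (−0.319) = +0.16 SD, so the slope contrast goes **against** i-VR by 0.16 SD

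Overall i-VR retention is 0.5 × 0.7 + 0.5 × 0.3 = 50%, the same as waitlist. Equal total attrition would not reveal the problem.

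| a / b | ρ | baseline gap (SD) | slope contrast against i-VR (SD) | raw 12-month gap (SD) |
|---|---|---|---|---|
| 50% / 50% | any | 0 | 0 | 0 |
| 60% / 40% | 0.5 | −0.16 | 0.08 | −0.08 |
| 70% / 30% | 0.3 | −0.32 | 0.22 | −0.10 |
| 70% / 30% | 0.5 | −0.32 | 0.16 | −0.16 |
| 70% / 30% | 0.7 | −0.32 | 0.10 | −0.22 |

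Swapping a and b reverses every sign.

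**4. The same data with all randomised patients.** Loss depends only on X, so the regression of Y on X among retained patients still has intercept 0 and slope ρ. FIML evaluates it at the full-arm baseline mean, which is 0: estimated 12-month mean 0, change 0, contrast 0. A simulation of 2 million gave 0.002 SD. Conditioning on baseline in the restricted set also gives about 0 (0.001 SD).

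**5. What the change does not cure.** Let true recovery be 50% in both arms, with i-VR retention 60% if recovered and 40% if not, and waitlist retention 50%. Observed recovery is 0.30/(0.30 + 0.20) = 60% vs 50%. With recovery scored as a follow-up score below its median and ρ = 0.5, FIML on all randomised patients is biased by −0.119 SD. The restricted set adjusted for baseline is biased by −0.120 SD. Counting missing as not recovered gives 0.5 × 0.6 = 30% vs 0.5 × 0.5 = 25%, which halves the false 10-point gap but does not remove it.

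**The case against.** The strongest reply is that only a wording conflict remains. Loss that depends on baseline alone does not distort an analysis that conditions on baseline. The plan includes covariates for pre-existing differences and unspecified adjustments for the block design, which balances on initial PTSD level. If those put baseline severity into the model as a conditioning variable, the illustrated bias largely disappears. That stands as a limit on size. However, the text names only background characteristics as covariates and treats the initial level as part of the modelled trajectory, so such conditioning is possible but not stated.

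Four stronger readings are tempting and are not supported:

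- **That half of the trial would be excluded.** A reader might infer this from "assuming 50% attrition rate". The Sample size section does not say when attrition occurs, although the Abstract's 200 randomised points to loss after allocation. A patient seen at any one wave stays in. Half is an upper bound.
- **That the rule creates a spurious benefit.** The raw 12-month mean suggests it, but for the slope contrast that the plan names, the same selection goes the other way. The documents fix neither direction nor size.
- **That outcome-dependent dropout shows the harm of this sentence.** Such loss biases the all-randomised analysis almost equally (step 5), so it cannot be charged to the analysis set.
- **That this is a completer analysis.** Nothing excludes patients for missed sessions or for stopping treatment. Selection is on having any follow-up interview.

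A further reply is that a full protocol or SAP may define the set differently. The absence of sensitivity analyses from an article is indeed no finding. Here, though, the article states the set, and it contradicts the article's own promise.

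**Conclusion.** The conflict holds. The analysis set is defined by a post-randomisation event, which is not the intention-to-treat analysis promised in the Abstract. Between 0 and about 100 of the 200 randomised patients could be excluded. In a growth model with baseline as the intercept, the restriction can make the intercepts unequal and bias the slope contrast in a way that FIML on all randomised patients would not. Under the assumed 70%/30% retention and correlation 0.5, the false slope contrast is about 0.16 SD against i-VR. It is 0 if retention does not vary with baseline, and it reverses sign if retention runs the other way. These figures rest on assumed retention rates and a two-time-point simplification. They show a mechanism, not an expected bias in this trial.

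**What to change.** Replace the sentence defining the analysis set with: *All randomised participants are analysed in the group to which they were allocated, whether or not they provided follow-up data.* Keep FIML, with the baseline measurement in the model. Report the set with at least one follow-up wave only as a sensitivity analysis.

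The cost is one sentence and one extra run. The baseline interview precedes randomisation, so the data needed are already collected. A missing-not-at-random check on the 12-month diagnosis, such as counting missing as not recovered, is optional. It would reduce, not remove, bias from loss that depends on the outcome.

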## Method

### Participants

Adult patients, aged 18–65, who arrive at a Level I emergency department (ED) following a motor vehicle accident (MVA) will be recruited to the study. Inclusion criteria were the ability to give informed consent and PTSD symptoms 2 weeks posttrauma; this will be assessed regarding all symptoms apart from the criteria of time. Exclusion criteria include suffering from, or have suffered from in the past, bipolar disorder, psychotic disorder, or substance abuse (as measured by the SCID); suffering from ongoing PTSD (as measured by the CAPS); loss of consciousness on arrival to the ED; suffering from another Axis I anxiety disorder that requires immediate treatment; and currently presents as a suicide risk.

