### Procedure

The telephone interview team will call suitable ED patients within 2 weeks of their traumatic event, and an initial telephone assessment will determine whether the individual indeed meets study criteria. After receiving verbal informed consent, subjects will be given the details of a secure Internet site, where they will be asked to fill out questionnaires. Subjects with a PCL-5 score over 33 will be telephoned for a second telephone assessment. During this assessment, the patient will be assessed with the Structured Clinical Interview for DSM-IV (SCID I) and Clinician-Administered PTSD Scale (CAPS-5). If the patient fulfills the inclusion criteria, the patient will be invited to join the RCT. Subjects who enter the trial will receive a detailed description of the study, and if interested in participating, they will sign informed consent. These clinical interviews will be carried out by the telephone interview team, who will remain blind to treatment condition.

Patients will be randomly assigned by computer to one of the two treatment arms. Assigning the participants to either treatment or control group will be done using block randomization to ensure comparable numbers of participants of same gender and same initial PTSD level in each group. Patients in the waitlist condition will fill out questionnaires via the secure Internet site once a week. These will be checked by a team member dedicated to this task, who will be able to contact these patients should a specific need arrive. Patients in the i-VR arm will receive a laptop computer, with the i-VR program loaded on. They will receive training on how to access it, and a time for the first i-VR session will be made. The five i-VR sessions will be with experienced CBT therapists; these are all clinical psychologists or clinical social workers, who have received postgraduate certification as CBT therapists. In addition, they are trained in trauma-focused CBT and have extensive experience in protocol-driven research trials. Therapists will receive weekly supervision from the PI.

Sessions will be taped with the consent of the patient, and this will be used for supervision purposes. In addition, a random 10% of sessions will be evaluated by external supervisors for fidelity to the treatment protocol.

Follow-up assessment will be conducted by the telephone interview team through clinical telephone interviews, at 2 weeks following the end of treatment, and again 6 and 12 months later (Fig. 3).

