### Research tools

*Self-Report Questionnaires*: These will be administered via a secure Internet site.BDI II: The Beck Depression Inventory II (Beck, Steer, & Brown, 1996) is a 21-item self-report questionnaire that has been widely used as a measure of depressive symptoms in trauma populations.PCL-5 (Weathers, Litz, et al., 2013): This is a 20-item self-report questionnaire, assessing PTSD symptoms according to DSM 5 (APA, 2013). A cut off score of 33 (Weathers, Litz, et al., 2013) indicates probable PTSD.

*Clinical interviews*: Patients will be assessed by telephone, before treatment and after treatment, and 6 and 12 months following the end of treatment. These interviews will be carried out by trained psychologists, who will remain blind to treatment condition. The following instruments will be used:SCID I: It (First, Spitzer, Gibbon, & Williams, 1996) is used to evaluate the current and lifetime presence or absence of Axis I disorders. The Hebrew version has been used in many studies. The SCID is considered to be the gold standard when evaluating Axis I disorders.CAPS-5: It (Weathers, Blake, et al., 2013) is a 30-item semistructured interview that confers a diagnosis of PTSD according to DSM 5 (APA, 2013) and a continuous measure of PTSD symptoms’ frequency and intensity.BDI: The Beck Depression Inventory (Beck et al., 1996) as described above. This will be administered as an interview.The Trimbos/iMTA questionnaire for Costs associated with Psychiatric illness, TiC-P (Van Roijen, Van Straten, Al, Rutten, & Donker, 2006). This is a 27-item self-report questionnaire, assessing both direct and indirect costs of psychiatric illness. This will be administered as an interview.

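### CAPS PTSD diagnosis hardly varies at the pretreatment wave because of the entry criteria, so the article's intercept-and-slope growth comparison does not suit the main outcome

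*Protocol article*

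**What the plan says.** **Entry.** The Participants section requires "PTSD symptoms 2 weeks posttrauma; this will be assessed regarding all symptoms apart from the criteria of time". Under Procedure, "Subjects with a PCL-5 score over 33 will be telephoned for a second telephone assessment". At that second call "the patient will be assessed with the Structured Clinical Interview for DSM-IV (SCID I) and Clinician-Administered PTSD Scale (CAPS-5"), and then "If the patient fulfills the inclusion criteria, the patient will be invited to join the RCT".

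**Waves.** Research tools states: "Patients will be assessed by telephone, before treatment and after treatment, and 6 and 12 months following the end of treatment". Only one interview precedes treatment, so the entry interview also supplies the first wave. The same section says that the CAPS-5 "confers a diagnosis of PTSD according to DSM 5 (APA, 2013) and a continuous measure of PTSD symptoms".

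**Analysis.** In Data analysis, "The main outcome variable is PTSD diagnosis according to the CAPS, at 12 months posttreatment". Severity of PTSD and depression symptoms is secondary. The principal method is a conditional latent class growth model comparing the arms' trajectories on each of five outcomes, which are not listed. If the hypotheses hold, "we expect the intercepts (the initial levels) of the growth curves in both groups to be identical", with steeper slopes under the intervention. No other test is named for the main outcome.

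**The concern.** The main outcome and the entry criterion measure the same thing with the same instrument. If nearly every randomised patient has the diagnosis at the first wave under the entry definition, that wave cannot separate the arms. Equality there follows from who was admitted and says nothing about what randomisation achieved.

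The growth comparison leans on that wave twice. It defines the initial level, and it anchors the slope by which benefit is to be judged. A yes/no outcome that starts at a ceiling, drops by the first follow-up and then levels off is poorly described by a straight line on the logit scale. The misfit passes into both the intercept and the slope. At stake is whether the named analysis can show the 12-month difference in recovery that the trial is sized to find.

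**Working it through.** **1. The plan's own figure.** Sample size section: recovery 30% against 70%, alpha 0.05, power 0.95, total 64. With a pooled-variance comparison of two proportions and no continuity correction,

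n per arm = [z(alpha)·√(2·p̄·(1−p̄)) + z(power)·√(p1(1−p1) + p2(1−p2))]² / (p1−p2)².

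Here p̄ = 0.5, and one-sided both z values are 1.645: (1.645 × 0.7071 + 1.645 × 0.6481)² / 0.16 = 31.06, so 32 per arm and 64 in total. The figure reproduces one-sided. The two-sided version gives 76, which the 100 patients expected for analysis still cover. The calculation compares two proportions at one time and uses no baseline value, so this point leaves it unchanged.

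**2. Variation at the first wave.** Under the entry definition the prevalence of the diagnosis is p = 1 in each arm, so p(1−p) = 0. If the time criterion were instead enforced and could not be met at 2 weeks (an assumption, since the article does not give its length), p = 0 and the variance is again 0. For 100 patients all coded 1, the log-likelihood of this wave alone at logit intercept a is −100·ln(1 + e^(−a)):

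| a | log-likelihood |
|---|---|
| 4 | −1.81 |
| 10 | −0.0045 |
| 20 | −0.0000002 |

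It rises without a maximum. Taken alone, the first wave gives no finite level and no information on a group difference. Only three of the four waves are informative for the diagnosis.

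**3. Fitting a line through all four waves.** Assumed inputs: 50 per arm; PTSD prevalence 1, 0.40, 0.34, 0.30 under treatment and 1, 0.80, 0.74, 0.70 under control, ending at the rates implied by the Sample size section; waves scored 0 to 3; independent observations. Model: logit(p) = b0 + b1·arm + b2·time + b3·arm·time.

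- Estimates: b0 = 2.65, b1 = −1.09 (p = 0.03), b2 = −0.68, b3 = −0.32 (p = 0.19).
- Fitted baseline: 1/(1 + e^(−2.65)) = 0.93 in control and 1/(1 + e^(−1.56)) = 0.83 under treatment, although both are 1.00.
- Fitted last wave: 0.65 and 0.19, against true values of 0.70 and 0.30.
- Direct comparison of the same data at 12 months, 15/50 against 35/50: Fisher p = 0.0001.

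**4. Sensitivity to the assumed shape and timing.**

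| Assumption | intercept difference p | slope difference p |
|---|---|---|
| waves 0–3, trajectories above | 0.03 | 0.19 |
| waves at assumed months 0, 2, 8, 14 | 0.002 | 0.26 |
| waves 0–3, flat at 0.30 and 0.70 after baseline | 0.07 | 0.06 |

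In all three cases the 12-month rates are 30% and 70%, yet the slope difference misses the 5% level. Much of the treatment effect is absorbed as an apparent baseline difference.

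**The case against.** The best reply is that the diagnosis may never have been meant for the growth model. The five outcomes are not listed, the Mardia normality check suits continuous scores, steeper slopes are read as symptom improvement, and both the main outcome and the sample size refer to a single time point. An article may leave the remaining detail to a fuller document. This limits the point: inclusion of the diagnosis is implied, not stated. It does not remove it, because the article itself calls the growth model the principal method, applies it to every one of the five outcomes and names no other test for its main outcome.

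Constancy at entry is also partly inferred. Participants names the CAPS only for excluding ongoing PTSD, and the one numeric threshold is on the PCL-5. But the CAPS-5 is given at the entry interview and the symptom criterion waives only time, so essentially no variation is the natural reading.

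A reader might infer three stronger things, which the documents do not support:

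- *The model cannot be estimated.* A growth intercept is estimated from all waves jointly, and the fit above converges with finite values.
- *The identical-intercept expectation is met whatever happens.* In the first illustration it fails, with p = 0.03. Nor does the article present it as a check of randomisation; balance is addressed by blocking on gender and initial PTSD level and by covariates.
- *The diagnosis is defined differently at follow-up.* The waiver appears only in the entry criterion and a DSM-5 diagnosis is used later, so this is possible. However, the article does not say which rule applies at follow-up.

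**Conclusion.** The point holds in limited form. On the natural reading of Participants, Procedure and Data analysis, the main outcome is essentially constant at the pretreatment wave, so that wave carries no information on a group difference and equality there comes from selection. If the named growth comparison is applied to the diagnosis with that wave included, it can misstate the starting levels and miss the effect: 0.83 against 0.93 when both are 1.00, and slope p = 0.19 when 12-month PTSD is 30% against 70%.

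Those figures rest on assumed trajectories, 50 per arm, independent observations and a fixed-effect linear logit, which simplifies the latent class model. They show what can happen and do not predict the trial's result. The fitted last-wave prevalences still differ clearly between arms (0.19 and 0.65), so it is the slope criterion named in the article that loses the effect. Continuous CAPS and depression scores, which can vary at baseline, and the sample size are not affected.

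**What to change.** For PTSD diagnosis:

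- leave the pretreatment wave out of the modelled outcome;
- model the post-treatment, 6-month and 12-month diagnoses under one stated definition that says how the time criterion is handled;
- take the group difference at 12 months as the main test;
- enter pretreatment CAPS-5 severity as a covariate.

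List the five outcomes, and limit the expectation of identical intercepts and steeper slopes to the continuous scores.

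The cost is a change of wording in the analysis text. Every variable is already collected, and no assessment or patient is added.
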